## **Trial Protocol**

### **Scientific Abstract**

Quitting smoking is the most effective way of reducing the risk of cancer. One way of helping people stop smoking is to provide them with free Nicotine Replacement Therapy (NRT; e.g., nicotine patch), such as when NRT is sent to people by postal mail as part of a mass distribution initiative. Our previous research indicated that the impact of the mailed NRT intervention on increasing quit rates in rural areas may be substantial. The current research project seeks to confirm this finding and to understand the social determinants of health driving these anticipated large effects. This information is essential in order to target limited health resources to regions that are most in need, and who are likely to experience the greatest benefit.

Telephone numbers will be randomly selected from across rural regions of Canada in order to recruit adult smokers interested in completing a smoking survey and willing to be interviewed again in 6 months. The survey will ask participants about their smoking history, demographic characteristics, and a hypothetical question: would they be interested in receiving the nicotine patch if this were provided to them free of charge? Half of the smokers interested in receiving nicotine patches will be selected by chance and offered the NRT package. The other half of smokers will not be offered the nicotine patches. In addition, the municipality where each participant lives will be identified and participant data will be linked to relevant municipal characteristics (e.g., smoking rates, availability of health services). Characteristics of the participants and the municipalities in which they live will be used to explain why the nicotine patch intervention has a larger impact in some rural regions compared to others.

The findings from the proposed RCT are timely and of high relevance as the distribution of nicotine patches has substantial potential to combat the public health problem of cigarette related cancer, other diseases, and premature death from tobacco use. Targeting such tobacco cessation initiatives to rural regions may substantially increase the impact and cost-effectiveness of this intervention, helping to optimize the use of limited prevention resources while aiming to save the maximum number of lives.

## Background

In Canada, smoking tobacco accounts for approximately 30% of all cancer deaths and is a risk factor for at least 18 types of cancer. Smoking is also a significant negative contributor to numerous other health conditions. Rates of smoking appear to have recently increased in Canada (15% in 2017 from 13% in 2015). Cessation plays an impactful role in the prevention of cancer, where 10 years after quitting the mortality rate from lung cancer is about half of that of a continuing smoker.

*Rates of smoking are higher in rural than in urban regions of Canada:* Over 6.3 million people live in rural regions of Canada and smoking prevalence is higher in rural compared to urban regions. Also crucial – tobacco cessation initiatives have been less successful outside of urban areas and provision of health care is challenging in areas of lower population density. Given that Canadian mortality rates are higher in rural than in urban areas, and that a significant component of this difference in mortality rates is due to modifiable risk factors, such as smoking, interventions targeting smoking in these regions could reduce these mortality inequalities. To reduce the health disparities associated with living in rural areas, new ways of promoting tobacco cessation are needed that are amenable to delivery over large geographic areas. The provision of free nicotine patches sent by postal mail is one such promising option.

*Effectiveness of NRT:* There has been extensive research evaluating the efficacy of NRT as a means to promote smoking cessation. A Cochrane review of 150 randomized trials involving NRT concluded that NRTs increase the rate of quitting smoking by 50 to 70%, irrespective of the clinical setting in which the smoker is treated.

*Evidence for the benefits of providing free NRT by postal mail:* There are mass distribution initiatives of free NRT ongoing in several countries, including the US and Canada (Ontario). Further, there is evidence that the distribution of free NRT is **cost-effective**, with the cost of \$179 per participant in the Canadian mass distribution initiative. Moreover, a promising aspect about mass distribution of NRT initiatives is that, while it is available to everyone, **vulnerable populations (whether due to mobility issues, or co-existing mental health concerns) are by far the most likely to respond to the initiative and request free NRT.** An additional point as an argument of the benefit of providing free NRT is that it removes a financial barrier to access of NRT for people with low socioeconomic status, a factor that often co-occurs with areas of high smoking rates. Thus, the proposed tobacco cessation initiative is an excellent means of targeting vulnerable populations.

*Targeting NRT distribution to regions that may benefit most:* Results from our mailed nicotine patch trial indicated that the impact of free NRT distribution may be unexpectedly large in rural areas (OR = 9.59). This effect size is substantial in comparison to that observed in our earlier work on NRT distribution that largely comprised participants from urban/suburban regions (OR = 2.65). While encouraging, this large effect size requires replication to increase confidence in the results because the sample size of participants from rural regions in our earlier trial was small and this was a secondary analysis.

*What other factors might predict a large impact of the NRT intervention?:* Understanding the regional factors driving the impact of the NRT intervention are essential as it points to a means of targeting limited public health resources to substantially increase the number of people quitting smoking. There is a substantial research tradition investigating individual factors predictive of smoking cessation, including some within the context of RCTs investigating tobacco cessation. Our analytic plan will allow for the consideration of these individual factors alongside other predictors of tobacco cessation. There is less existing research investigating municipal-level factors related to tobacco cessation. It is well known that the prevalence of smoking in adults varies across different provinces and territories of Canada (ranging from 17% in British Columbia to 63% in Nunavut). Importantly, there are also substantial variations in smoking rates across municipal districts within these larger regions of Canada (e.g., in Ontario, rates of smoking in adults ranged from 15.4% to 44.7% between municipalities, with the highest rates generally in rural municipalities). The current project will nest an RCT within a survey with linked municipal-level data. This multidisciplinary approach will allow us to determine the impact of municipal characteristics on the effectiveness of the NRT intervention.

### **Principal research questions**

**Question 1:** Will an intervention of known efficacy – the distribution of free-of-cost nicotine patches sent by postal mail – have a large impact in rural regions of Canada?

**Primary Hypothesis:** Participants receiving the NRT package will display significantly greater quit rates (30 day abstinence) at 6-month follow-up as compared to those not offered the NRT package.

Our analysis plan also includes a test whether **participant gender moderates** the impact of the intervention.

**Question 2:** What other factors that systematically vary between municipalities impact the effectiveness of the nicotine patch intervention? We will use the work of Corsi et al. (2012, 2013), as well as work by co-authors [name] and [name] identifying geospatial factors related to smoking, on the community-level factors related to smoking in Canada to identify relevant factors [prevalence of smoking, availability of health services, average socioeconomic status (SES), population density, region of Canada, tobacco retailer density, NRT distributor density (e.g., pharmacy, grocery store)].

While an extended set of municipal factors listed here will be collected (and examined for their predictive value as part of our secondary analyses), we focus on two contextual factors that we believe are key to why the NRT intervention may be especially impactful in rural settings.

**Prevalence of Smoking Hypothesis:** The impact of the NRT intervention will be larger in municipalities where there is a higher prevalence of smoking compared to municipalities where the prevalence of smoking is lower.

*Smoking is more prevalent in rural regions than in urban regions.* Because of this known higher prevalence of smoking rates in rural versus urban regions, and because the impact of the

NRT intervention appears to be unexpectedly large in rural regions, the proposed research predicts that the impact of the mailed nicotine patch intervention will be larger in regions with higher smoking rates versus those in regions with lower smoking rates. There is relevant existing research that supports this postulated differential impact. As smoking rates in an area decline, it has been suggested that those remaining in the population are more hardcore smokers (i.e., less likely to want to quit), whereas in areas with a higher smoking prevalence you are more likely to have smokers in the population who want to quit.

**Lack of Health Services Hypothesis:** The impact of the NRT intervention will be larger in municipalities where there is less availability of health services compared to municipalities where there is a higher availability of health services.

*Health services* are more difficult to provide in areas of low population density (i.e., rural regions). The provision of some type of help (in this case a mailed tobacco cessation aid that is well suited for a rural region) will display a larger impact in a situation where there is a lack of other services available than in one that is relatively rich in available health services.

## **Methods**

**Study procedure:** A two-stage recruitment process will be employed, in the context of a general population survey with a 6-month follow-up. Random digit dialling of telephone numbers from rural regions of Canada will identify households with adult (age 18 or over) smokers who smoke 10 or more cigarettes a day and who are willing to take part in a smoking study that involves two interviews. If low recruitment numbers are experienced with random digit dialling, online advertising methods (e.g. Facebook/Instagram, Kijiji volunteer section) will be used to collect telephone numbers of current adult smokers, living in rural regions who are interested in participating in a telephone survey about their smoking experiences. Should recruitment be lower than expected and the online advertising is used, interested individuals will be able to click on a link in the advertisement which will take them to a brief screener. Those found eligible (i.e. 18 years of age or older, currently smoking 10 or more cigarettes and living in an area with a rural postal code – identified using the first 3 alphanumeric Forward Sortation area code) will be asked to provide consent to be contacted by the third-party vendor contracted to complete the interviews. Individuals will be asked to provide a telephone number for this purpose (no names or other identifying information will be collected). Telephone numbers will be sent via secure file transfer to the vendor. Collection of verbal consent and baseline interview will proceed as described hereafter.

Participants will be paid \$20 for the completion of each of the baseline and 6-month follow-up (payment will be made by cheque – allowing us to collect participant postal codes in order to link participant data to municipal region). Verbal consent will be obtained as the initial contact is by telephone. Only one person per household will be recruited to participate, using the method where the current smoker with the next birthday in the household is asked to participate. Both cell phone and landline numbers will be contacted. Interviews, and the remainder of the study, will be offered in both English and French. Residence of participants in rural regions will be confirmed by postal code matching. As part of the baseline survey, eligible subjects will be identified for the second recruitment – randomization of smokers into experimental and control

conditions to be offered versus not offered Nicotine Patches. A randomized half of the eligible participants will be assigned to the experimental condition and asked for their permission to have Nicotine Patches sent to their home. The 6-month follow-up survey will be conducted 6-months after the baseline survey. A letter will be sent to the participant in the 2 weeks prior to the telephone survey to notify the participant of its occurrence.

*Randomization:* Interviews will be conducted using computer assisted telephone interview (CATI) technology. At the end of the baseline interview, eligible subjects will be allocated to experimental and control conditions using block randomization (1:1 ratio) built into the CATI program (no stratification or minimization is necessary given the large proposed sample size in this trial).

*Protecting against sources of bias:* The interviewers conducting the baseline and 6-month post-intervention follow-up survey will be blind to experimental condition at the time the key outcome questions are asked. Further, while it is possible that a participant might ‘unblind’ themselves to an interviewer by volunteering that they used the nicotine patch, this is still unlikely to have an impact as the interviewers will be part of a separately contracted telephone survey research firm and will not be aware of the hypotheses of this research trial or be involved in the randomization process.

**Inclusion criteria:** The baseline telephone survey will identify adults (age 18 or over) who smoke 10 or more cigarettes a day, and who are willing to take part in a smoking study that involves two interviews. As part of the baseline survey, all participants will be asked a series of questions to assess their level of interest in receiving free NRT: “The Ministry of Health is considering different ways to help people stop smoking. One option would be to provide interested smokers with free Nicotine Patches. If Nicotine Patches were offered for free, would you be interested in receiving them?” Those who say “yes” will then be asked if they would use the Nicotine Patch to quit smoking. Those who say “yes” to this question will be asked if they would begin to use the Patch within 1 week of receiving it. A “yes” to this question will lead to being asked if they would be willing to have the Patch sent to their home. These items have been employed in our previous research trial of mailed NRT (albeit largely in urban regions).

*Exclusion criteria for randomized trial:* Having a health condition contraindicating NRT use without the supervision of a doctor (i.e., being pregnant; having a serious heart or circulation problem, not including high blood pressure).

### ***Interventions***

*Intervention group:* Participants randomized to the intervention group will be asked, at the end of the baseline survey, if they want to be sent a free, 5-week supply of Nicotine Patches (example wording: “As part of a pilot trial, the Centre for Addiction and Mental Health has a supply of Nicotine Patches to distribute to interested smokers. You told us that you would be interested in receiving a free supply of Nicotine Patches. Do we have your permission to mail them directly to you at your home?”). Those agreeing will have the NRT mailed to their home the week after their baseline interview. A 5-week program of Nicotine Patches will be sent (3 weeks of Step 1 [21 mg of nicotine]; 1 week of Step 2 [14 mg of nicotine]; 1 week of Step 3 [7 mg of nicotine]). Participants will be instructed to use 1 patch per day. The mail-out will also contain a letter that advises participants to talk to their doctor if they have questions or concerns about the use of

NRT. While NRT is available over the counter, and is low-risk, should any adverse events be reported, the principal investigator will review them with an MD or pharmacist. Once randomly assigned to this condition, participants will be counted as part of the intervention group whether they agree to accept the NRT or not (intent-to-treat approach).

*Control group:* Participants randomly assigned to the control group will not be offered Nicotine Patches at the end of the baseline survey. An advantage of the design procedure to be employed in this trial is that participants in the control group will not have the expectation that they will receive NRT. Thus, their smoking outcomes at 6-month post-intervention follow-up will reflect a true natural history comparison to the outcomes of participants in the experimental group.

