*Content of 6-month post-intervention follow-up survey:* Participants will be asked their current smoking status, including length of time without smoking in order to assess the primary outcome variable. Participants who have not quit will be asked how many cigarettes per day they currently smoke and their intentions to quit smoking; how soon after waking they smoke their first cigarette; and if, since their baseline interview, they have stopped smoking for even one day because they were trying to quit. Participants in the experimental group will be asked if they received free NRT and, if they did, to evaluate their experiences with NRT and to elaborate on their efforts to quit smoking. These questions will include items asking whether the participants used the NRT (none, some, all) and what they did with the NRT that they did not use themselves. These questions will be asked after the core smoking status outcome measures have been assessed. Participants in the control group will also be asked about their use of NRT but the questions will be framed to reflect purchase of NRT from sources other than this ongoing study.

Participants in both conditions will also be asked about their use of other smoking cessation aids and services, including electronic cigarettes, self-help/online methods, as well as participation and/or receipt of various forms of advice and counselling from family physicians, smoking cessation specialists, or other healthcare providers. As some individuals are known to initiate use of other tobacco products after stopping use of conventional cigarettes, such as cigars or non-combustible products such as smokeless tobacco or electronic cigarettes, participants who report smoking abstinence will be asked if they currently use other tobacco or nicotine containing products. This will allow us to examine whether people who quit cigarettes compensate with other forms of nicotine delivery.

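### Adverse events are captured only by spontaneous report: no described follow-up item names harm in either arm, and the one interview after mailing comes about 17 to 20 weeks after the patch course would end

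*Protocol*

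**What the plan says.** The protocol's only adverse-event provision is in Interventions, in the intervention-group paragraph: "should any adverse events be reported, the principal investigator will review them with an MD or pharmacist". The same sentence gives the reason for light monitoring: "While NRT is available over the counter, and is low-risk". The control-group paragraph has no counterpart.

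On timing, the same section says "Those agreeing will have the NRT mailed to their home the week after their baseline interview" and "A 5-week program of Nicotine Patches will be sent". The package includes "a letter that advises participants to talk to their doctor if they have questions or concerns".

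Methods (Study procedure) describes two interviews, one at baseline before any patches are sent and one 6 months after baseline. The only other contact it describes after mailing is a letter announcing the second call, sent in the 2 weeks before it.

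Measures lists the content of the 6-month survey in some detail. Intervention participants who received NRT are asked "to evaluate their experiences with NRT and to elaborate on their efforts to quit smoking", how much they used and what became of the rest. Controls are asked about NRT obtained from other sources. No described item in either arm names side effects, health problems or medical visits. The health questions that include contraindications to NRT are listed for baseline and not for follow-up.

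**The concern.** The provision names who will review an event but not how an event reaches them. No active question, reporting route or time limit is described. What the study learns about harm therefore depends on participants volunteering it, either unprompted during use or months later in answer to a general question about their experience. Spontaneous reporting usually yields fewer events than direct questioning.

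Collection also differs by arm. The one item that could bring out a harm goes only to intervention participants who received patches, so any events found that way have no control-arm comparator. Onset after baseline of a condition in the trial's own exclusion criteria (pregnancy, or a serious heart or circulation problem) is not picked up by any described item.

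The stake is how a harm count from this trial can be read. The trial is meant to inform the targeting of mailed patches to rural regions. If few events appear, the data as collected could not separate few harms from few people asked.

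**Working it through.** There is no stated safety figure to reproduce. The check is one of timing, coverage and content.

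**Inputs**
- Mailing: 1 week after baseline (Interventions).
- Course length: 5 weeks (Interventions).
- Delay from receipt to first use, s: 0 to 1 week. Inclusion criteria ask whether the person would start within a week of receiving the patches; this is a stated intention, not observed use.
- Delivery time, d: not given; assumed 0 to 2 weeks.
- Follow-up interview: 6 months after baseline, about 26 weeks (Methods).
- Attrition: 20%, with 290 per group (Power calculations).

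**Gap between end of course and interview**

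Gap = 26 − (1 + d + s + 5)

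| Delivery d (weeks) | Start delay s (weeks) | Course ends (week) | Gap (weeks) |
|---|---|---|---|
| 0 | 0 | 6 | 20 |
| 0 | 1 | 7 | 19 |
| 1 | 0 | 7 | 19 |
| 1 | 1 | 8 | 18 |
| 2 | 0 | 8 | 18 |
| 2 | 1 | 9 | 17 |

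The range is 17 to 20 weeks. Taking 6 months as 26.09 weeks (365.25 / 2 / 7) adds less than 0.1 week to each row.

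**Coverage**
- Not interviewed at 6 months: 290 × 0.20 = 58 intervention participants.
- Interviewed: 290 × 0.80 = 232.

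The 290 are everyone randomised to the intervention, including those who decline the patches, so the number exposed is at most 290 and is not known in advance.

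**Content of the 6-month interview, by arm**

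| Topic | Intervention | Control |
|---|---|---|
| Use of NRT | Asked | Asked, for other sources |
| Evaluation of experience with NRT | Asked of those who received it | Not described |
| Named side effect, health problem or medical visit | Not described | Not described |
| New onset of an exclusion condition | Not described | Not described |

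**The case against.** The strongest reply is proportionality. The patch is sold over the counter, the protocol calls it low-risk, people with the named contraindications are excluded, and any reported event is reviewed with an MD or pharmacist. No research question, hypothesis or analysis concerns safety, so the lack of a between-arm harm comparison fails no stated aim. This stands, and it limits the severity. It does not supply a means of finding events.

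Several stronger readings are tempting, and the document does not support them:
- **That no report can reach the study.** The mail-out letter is only summarised and the consent and contact pages are not in the public text. A study telephone number may exist there.
- **That nobody is asked anything bearing on harm.** The evaluation item may bring out some harms among patch recipients, and the interview script itself is not shown. The supportable statement is that no described item names harm.
- **That the interview is the only planned contact.** The notice letter precedes it, and the Analysis Plan mentions biochemical validation, whose timing is not described. It is the only described interview after mailing. Likewise, attrition means loss to that interview, not loss of all contact.
- **That no event would be acted on in time.** Spontaneous reports would be reviewed and participants are pointed to a doctor. What is missing is a stated route and timing.
- **That rural participants have no doctor to turn to.** The remark that services "are more difficult to provide in areas of low population density" belongs to a hypothesis about what modifies the effect. It does not describe participants' own access.
- **That the sponsor will present a near-zero count as proof of safety.** Nothing in the protocol says so; low risk is a premise there, not a planned conclusion.

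**Conclusion.** The point holds in a limited form. As described, adverse events are captured by spontaneous report only, no follow-up item names harm in either arm, and the single post-mailing interview falls about 17 to 20 weeks after the course would end. About 58 of 290 intervention participants would miss that interview. Under-counting is therefore likely, what is collected would be asymmetric between arms, and a low count should not be read as evidence of few harms. The amount of under-counting cannot be calculated from the document.

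The 17 to 20 weeks rests on the assumed delivery time and on participants starting within a week and using one patch a day; a later start would shorten the gap. The figure of 58 rests on the protocol's own attrition rate.

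This is a cheap improvement to data collection. It does not threaten the primary analysis. How harms are collected belongs in a protocol, so the point is not one left to the statistical analysis plan.

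**What to change.** 1. Add to the existing 6-month telephone script a short, fixed set of questions, worded identically in both arms: any new health problem since baseline; any hospital or emergency visit; and onset since baseline of the conditions already listed as exclusions. Record the timing of each relative to any NRT use. Place them after the primary outcome items, so that interviewers remain blind when those are asked. Asking about any new health problem, rather than problems attributed to a cessation product, keeps the question comparable for controls, who are sent none.
2. Report the answers by arm, with the number of participants actually asked as the denominator, and state that recall is several months after use.
3. Confirm that the mail-out letter or consent script gives a study contact for problems during patch use, and add one if it does not. The 6-month items improve counting and comparison but cannot make detection timely; only this step bears on reports during use.

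The cost is about 1 to 2 minutes per call and a minor amendment to the script, and possibly to the letter.
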